## Abstract

Traumatic brain injury (TBI) is a global public health condition that causes cognitive and behavioral deficits. This protocol assesses the potential of quantitative electroencephalogram (EEG) biomarkers, associated with inflammatory indicators, to predict mortality and functional recovery in patients with severe TBI. Through continuous monitoring and analysis of abnormal brain activity patterns, the protocol aims to personalize therapeutic interventions and improve patient quality of life. This randomized clinical trial includes 84 adult participants with severe TBI, followed at different stages of recovery, using validated scales for functional and predictive analysis. Traumatic brain injury (TBI) is a globally impactful public health condition characterized by initial brain injuries caused by traumatic forces, leading to cognitive and behavioral deficits. The trauma triggers inflammatory and neurochemical changes that exacerbate neuronal damage, resulting in neuropsychiatric complications. The use of electroencephalogram (EEG), particularly in its quantitative form (QEEG), is crucial for patients with severe TBI, as it allows early detection of abnormal brain activity patterns, such as slow waves, which indicate a worse prognosis. This continuous monitoring, combined with inflammatory biomarkers, guides personalized therapeutic interventions and improves the prediction of clinical outcomes, contributing to patient quality of life.

Specifications table

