## Background

Traumatic Brain Injury (TBI) remains a global health challenge, with high incidence rates in both developed and emerging economies [1,2]. Approximately 70 million people experience TBI annually, with 11% classified as severe [3,4]. In Brazil, between 2008 and 2019, the average annual incidence of TBI-related hospitalizations exceeded 131,000, with severe cases showing a hospital mortality rate of over 30%. TBI is the fifth leading cause of death among individuals aged 15–29 and the third among those aged 30–44, largely attributed to traffic accidents [5,6]. The Southeast region of Brazil reported the highest absolute incidence, with 648,447 cases during this period [7]. Effective clinical decision-making for moderate-to-severe TBI patients in intensive care units (ICUs) remains a significant challenge [8,9].

TBI is a complex condition that triggers substantial physiological changes, primarily an exaggerated inflammatory response. This inflammation often leads to secondary brain injuries, exacerbating neurological and functional complications [10,11]. Early Electroencephalography (EEG) monitoring at ICU admission is increasingly recognized as a valuable tool for assessing prognosis in severe TBI patients [8,9]. EEG provides real-time insights into brain activity, identifying specific patterns associated with injury severity and long-term outcomes [[12], [13], [14]].

EEG offers detailed information on cerebral function, including the detection of abnormal patterns such as diffuse slow waves and epileptiform activity. These abnormalities are linked to unfavorable outcomes, including cognitive deficits and a higher risk of post-traumatic epilepsy [[15], [16], [17]]. Additionally, EEG enables spatial analysis of electrical brain activity, highlighting asymmetries or regions of inactivity that correlate with neurological prognosis [18,19].

Despite the emphasis on acute-phase EEG monitoring, the subacute phase—post-ICU discharge—remains underexplored. Current studies provide a foundational understanding of EEG's relevance but lack focus on its application during recovery phases, where it may provide critical insights into functional recovery [20,21]. Addressing this gap is essential to advancing diagnostic accuracy and guiding therapeutic interventions for TBI patients.

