## Description of protocol

This study aims to contribute to the understanding of the incidence of TBI and its associated biomarkers in a trauma care setting, with a particular focus on electroencephalography (EEG) as a potential diagnostic tool for early detection and monitoring of TBI. By integrating EEG data, the study seeks to provide valuable insights into the relationship between brain electrical activity and TBI, ultimately advancing clinical outcomes in the management of TBI patients.

This prospective cohort study will be conducted at a trauma reference hospital in Vitória, Espírito Santo, Brazil. The study population will include all patients admitted with traumatic injuries, who will be monitored by researchers through daily entries in their medical records. This will enable the identification of cases of traumatic brain injury (TBI) and determine the eligibility of patients for inclusion in the study. The inclusion and exclusion criteria are detailed in Table 1. Informed consent and comprehensive details about the study protocol will be provided to participants at the time of the first data collection, ensuring full understanding of the research procedures and objectives.

**Table 1 tbl0001:** Inclusion and exclusion criteria for the study.

Inclusion criteria	Exclusion criteria
Adults of both sexes, aged 18 or older	Under 18 years old
Glasgow Coma Scale (GCS) ≤ 8 at any time during hospital stay	Open TBI
Admitted to an Intensive Care Unit (ICU)	History of previous neurological diseases
Informed consent signed	History of previous psychiatric diseases

Sample size estimation was based on a two-tailed hypothesis test with a medium Pearson correlation coefficient (r = 0.3), a significance level (α) of 0.05, and a statistical power (1 - β) of 0.80. Using these parameters, a target sample size of 84 individuals was determined to provide adequate power for detecting clinically meaningful relationships between variables. The sample size calculation was performed using GPower software [22], a widely used tool for power analysis in experimental design.

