## Data collection protocol

The EEG data collection protocol will involve monitoring patients with severe traumatic brain injury (TBI) during the subacute phase of the trauma. The subacute phase is defined as beginning on the seventh day following the traumatic event [[23], [24], [25]]. EEG recordings will be performed immediately after the patient's transfer from the intensive care unit (ICU) to the hospital ward. This timing was chosen to account for the complex and dynamic nature of the ICU environment, while the hospital ward is expected to offer a more stable and controlled setting for optimal EEG acquisition. The subacute phase was selected because, in comparison to the acute phase, patients are generally more stable during this period, which is also when key physiological recovery processes and neuronal reorganization typically occur [[26], [27], [28]].

To comprehensively assess the functional and cognitive status of patients throughout the study, functional scales will serve as a critical component for comparing and validating the predictive potential of EEG in relation to TBI events. These functional scales, as detailed in Table 2, will be administered at key time points: ICU discharge, hospital discharge, and at three, six, and twelve months post-TBI.

**Table 2 tbl0002:** Description of functional scales.

Scale	Description
Glasgow Coma Scale (GCS)	Assesses the patient's level of consciousness based on three parameters: eye opening, verbal response, and motor response. The score ranges from 3 to 15, with lower scores indicating more severe coma.
Dementia Rating Scale (DRS)	Used to assess cognitive function in dementia patients. The score is determined by the patient's performance on memory, orientation, and ability to perform daily activities. The score ranges from 0 to 144, with lower scores indicating greater severity.
Functional Independence Measure (MIF)	Assesses the functional independence level of patients in daily activities such as eating, dressing, and mobility. Scores range from 18 to 126, where 18 indicates total dependence and 126 indicates total independence.
Functional Ambulation Categories (FAC)	Measures the patient's ability to walk based on the support needed. Categories range from 0 (no walking) to 5 (independent walking).

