### EEG protocol

The EEG protocol will be performed with the patient in a resting, relaxed, and awake state, with eyes closed. EEG recordings will be conducted using the Startism 20 system (Starstim® tES-EEG systems), a 20-channel device with specialized electrodes designed for EEG monitoring (Fig. 1). The settings will include a time constant of 0.3 seconds and a high-frequency cutoff at 30 Hz. To minimize potential artifacts that could compromise the quality of the recordings, the EEG will be performed in a quiet environment with low lighting to ensure optimal conditions.

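### Mortality in severe TBI is named as a prediction target, but the only EEG described is recorded after transfer to the ward, so at best mortality conditional on surviving to the ward can be studied

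*Protocol article*

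**What the plan says.** The Abstract of the protocol article sets the aim: EEG biomarkers, together with inflammatory indicators, are to "predict mortality and functional recovery in patients with severe TBI".

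The Data collection protocol section fixes when the predictor is measured. The recording follows "transfer from the intensive care unit (ICU) to the hospital ward", and "The subacute phase is defined as beginning on the seventh day following the traumatic event". No earlier EEG is described.

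Table 1 (Description of protocol) defines the population by age, ICU admission, consent and "Glasgow Coma Scale (GCS) ≤ 8 at any time during hospital stay". Survival to the ward is not among the criteria.

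The Background gives the only mortality figure, "severe cases showing a hospital mortality rate of over 30" per cent. It is not split into ICU and ward deaths.

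The outcome scales (Table 2) are scheduled at ICU discharge, at hospital discharge, and at 3, 6 and 12 months. As described, none of the five has a value for death. The Statistical analysis section plans binomial logistic regression and ROC curves for clinical outcomes and does not name the binary outcome.

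**The concern.** A prognostic model applies to the patients in whom its predictor could be measured. Here that means patients who have left the ICU alive, whereas the abstract speaks of severe TBI as a whole. Every death before ward transfer lies outside the model.

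Two things are at stake. First, an AUC for death estimated in ICU survivors could be reported, and used to guide treatment, as mortality prediction in severe TBI. Second, the deaths that do occur after the EEG may be few, and they have no score on any scale in Table 2. Unless they are given a place, the worst outcomes could be treated as missing in the functional analyses.

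**Working it through.** **The plan's own sample size.** Inputs from Description of protocol: r = 0.3, two-sided α = 0.05, power 0.80. The exact power of the Pearson test is 0.7955 at n = 83 and 0.8003 at n = 84, so the stated 84 is reproduced. The Fisher z approximation agrees within rounding: ((1.960 + 0.842)/0.3095)² + 3 = 84.9. The figure is right for a correlation. It was not derived for a mortality model.

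**Deaths with no EEG.** Inputs: hospital mortality 30% (Background, where it is a lower bound) and 84 patients recorded. The share s of hospital deaths that occur before ward transfer is not in the documents and is assumed. It is also assumed that every patient who reaches the ward is recorded.

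ICU patients needed: N = 84/(1 − 0.30·s). Deaths without EEG: N × 0.30·s. Hospital deaths left among the 84: N × 0.30·(1 − s).

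| Assumed s | N | Deaths without EEG | Hospital deaths among the 84 |
|---|---|---|---|
| 30% | 92.3 | 8.3 | 19.4 |
| 50% | 98.8 | 14.8 | 14.8 |
| 70% | 106.3 | 22.3 | 9.6 |
| 90% | 115.1 | 31.1 | 3.5 |

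Even if only 30% of hospital deaths come before the ward, about 8 deaths have no EEG.

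**Precision of a mortality AUC.** Assume that 5% to 10% of the 84 die after the EEG, that is 4.2 to 8.4 deaths. Take a true AUC of A = 0.75 and the Hanley-McNeil variance, with n₁ deaths and n₀ survivors:

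SE² = [A(1 − A) + (n₁ − 1)(Q₁ − A²) + (n₀ − 1)(Q₂ − A²)]/(n₁n₀), where Q₁ = A/(2 − A) = 0.600 and Q₂ = 2A²/(1 + A) = 0.643.

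| Deaths / survivors | SE | 95% half-width | Lower limit |
|---|---|---|---|
| 8 / 76 | 0.103 | 0.20 | 0.55 |
| 6 / 78 | 0.118 | 0.23 | 0.52 |
| 4 / 80 | 0.144 | 0.28 | 0.47 |

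The interval is wide throughout but falls below 0.5 only at about 4 deaths. At 15% or 20% mortality after the EEG the half-width is about 0.16 or 0.14. With the five bands of Table 3 as predictors, 4.2 to 8.4 deaths give 4.2/5 = 0.8 to 8.4/5 = 1.7 events per predictor.

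**Scale ranges as described in Table 2.** GCS 3 to 15, DRS 0 to 144, MIF 18 to 126, FAC 0 to 5, RLA levels I to VII. Each describes a living patient. If 5% to 10% of patients had no score and were left out, power for r = 0.3 would fall from about 0.80 to 0.77 or 0.75 (Fisher z). That loss is modest. The larger matter is that the patients without a score would be those with the worst outcome.

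**The case against.** The best defence is that the post-ICU focus is open and reasoned. The Background calls the subacute phase after ICU discharge underexplored, and the Data collection protocol explains why the ward is preferred for recording. The aims in the specifications table and at the end of the Background name prognosis, outcomes and functional recovery, not mortality. As a prediction target, mortality appears only in the abstract, so the defect could be called one overreaching phrase. This stands in part: the remedy is mainly one of wording. But the abstract is where the claim will be read, and no analysis plan can supply an EEG for a patient who died before the only recording.

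Some stronger readings are tempting, but the documents do not support them:

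- A reader might infer that most deaths are excluded, or that 36 of 120 admissions (84/0.70 = 120) never have an EEG. That figure needs every hospital death to fall before ward transfer. No ICU/ward split is given.
- A reader might infer that a mortality AUC could not be told apart from chance. Under the assumed 5% to 10%, this happens only at the lowest count.
- A reader might infer that later deaths are dropped from the functional models. No passage says so. Vital status could be a binary outcome in the planned logistic regression, and the coding may sit in a plan that is not shown.
- A reader might infer that recording "with the patient in a resting, relaxed, and awake state, with eyes closed" removes the least responsive survivors. This is a recording condition. Table 1 has no such exclusion, and no passage says that patients who cannot comply are left out.
- A reader might infer that nothing is known of patients before ICU discharge. Daily record review and clinical data from the hospital stay are planned, so deaths before the ward should be countable.

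**Conclusion.** The point holds in this form: the stated target, mortality in severe TBI, does not match a predictor first measured after ICU survival. This follows from the text alone. At best the study addresses mortality conditional on reaching the ward, and the cited hospital mortality of over 30% does not describe the analysed cohort.

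The size rests on assumptions. About 8 to 31 deaths would have no EEG per 84 recorded patients if 30% to 90% of a 30% hospital mortality precedes ward transfer. If 5% to 10% die after the EEG, a mortality AUC of 0.75 would have a half-width of about 0.28 to 0.20, which is imprecise but not always compatible with 0.5. The lack of a death value on the five scales, as described, is a fact of Table 2. How deaths are then handled is not known from the article.

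**What to change.** 1. Restate the objective and target population as prognosis after ICU discharge in patients with severe TBI who survive to the ward. Label any mortality result as exploratory post-ICU mortality.
2. State that a death after the EEG counts as an unfavourable (worst) outcome in the binary functional models and is not treated as missing.
3. Report the number of deaths before ward transfer in the patient flow, using the record review already planned.

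The cost is a narrower claim and a functional outcome that has to be read as a composite of death and poor function. No extra visits or recordings are needed.

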**Table utbl0001:** 

Subject area:	Neuroscience
More specific subject area:	Traumatic Brain Injury
Name of your method:	Data Colect Method
Name of your protocol:	Inflammatory EEG Biomarkers in TBI
Reagents/tools:	TDCS/EEG HD Startsmis32
Experimental design:	This will be a randomized clinical trial of the prospective cohort type conducted in parallel with EEG monitoring.
Trial registration:	Informed consent was obtained from the participants.
Ethics:	Informed consent was obtained from all patients after patient eligibility was confirmed. The entire research project was submitted to the Research Ethics Committee of the Federal University of Espírito Santo, and approval was obtained in accordance with substantiated opinion number 4222,002.
Value of the Protocol:	The protocol aims to evaluate the predictive potential of EEG biomarkers in prognosis, outcomes, and functional recovery of patients with severe TBI, through comparison with a gold standard method.

## Background

Traumatic Brain Injury (TBI) remains a global health challenge, with high incidence rates in both developed and emerging economies [1,2]. Approximately 70 million people experience TBI annually, with 11% classified as severe [3,4]. In Brazil, between 2008 and 2019, the average annual incidence of TBI-related hospitalizations exceeded 131,000, with severe cases showing a hospital mortality rate of over 30%. TBI is the fifth leading cause of death among individuals aged 15–29 and the third among those aged 30–44, largely attributed to traffic accidents [5,6]. The Southeast region of Brazil reported the highest absolute incidence, with 648,447 cases during this period [7]. Effective clinical decision-making for moderate-to-severe TBI patients in intensive care units (ICUs) remains a significant challenge [8,9].

TBI is a complex condition that triggers substantial physiological changes, primarily an exaggerated inflammatory response. This inflammation often leads to secondary brain injuries, exacerbating neurological and functional complications [10,11]. Early Electroencephalography (EEG) monitoring at ICU admission is increasingly recognized as a valuable tool for assessing prognosis in severe TBI patients [8,9]. EEG provides real-time insights into brain activity, identifying specific patterns associated with injury severity and long-term outcomes [[12], [13], [14]].

EEG offers detailed information on cerebral function, including the detection of abnormal patterns such as diffuse slow waves and epileptiform activity. These abnormalities are linked to unfavorable outcomes, including cognitive deficits and a higher risk of post-traumatic epilepsy [[15], [16], [17]]. Additionally, EEG enables spatial analysis of electrical brain activity, highlighting asymmetries or regions of inactivity that correlate with neurological prognosis [18,19].

Despite the emphasis on acute-phase EEG monitoring, the subacute phase—post-ICU discharge—remains underexplored. Current studies provide a foundational understanding of EEG's relevance but lack focus on its application during recovery phases, where it may provide critical insights into functional recovery [20,21]. Addressing this gap is essential to advancing diagnostic accuracy and guiding therapeutic interventions for TBI patients.

This protocol seeks to evaluate the predictive potential of EEG biomarkers for prognosis, clinical outcomes, and functional recovery in severe TBI patients. By comparing EEG findings with gold-standard outcomes, this study aims to enhance understanding of the role of EEG in managing TBI and contribute to improved clinical care and recovery strategies.

## Description of protocol

This study aims to contribute to the understanding of the incidence of TBI and its associated biomarkers in a trauma care setting, with a particular focus on electroencephalography (EEG) as a potential diagnostic tool for early detection and monitoring of TBI. By integrating EEG data, the study seeks to provide valuable insights into the relationship between brain electrical activity and TBI, ultimately advancing clinical outcomes in the management of TBI patients.

This prospective cohort study will be conducted at a trauma reference hospital in Vitória, Espírito Santo, Brazil. The study population will include all patients admitted with traumatic injuries, who will be monitored by researchers through daily entries in their medical records. This will enable the identification of cases of traumatic brain injury (TBI) and determine the eligibility of patients for inclusion in the study. The inclusion and exclusion criteria are detailed in Table 1. Informed consent and comprehensive details about the study protocol will be provided to participants at the time of the first data collection, ensuring full understanding of the research procedures and objectives.

**Table 1 tbl0001:** Inclusion and exclusion criteria for the study.

Inclusion criteria	Exclusion criteria
Adults of both sexes, aged 18 or older	Under 18 years old
Glasgow Coma Scale (GCS) ≤ 8 at any time during hospital stay	Open TBI
Admitted to an Intensive Care Unit (ICU)	History of previous neurological diseases
Informed consent signed	History of previous psychiatric diseases

Sample size estimation was based on a two-tailed hypothesis test with a medium Pearson correlation coefficient (r = 0.3), a significance level (α) of 0.05, and a statistical power (1 - β) of 0.80. Using these parameters, a target sample size of 84 individuals was determined to provide adequate power for detecting clinically meaningful relationships between variables. The sample size calculation was performed using GPower software [22], a widely used tool for power analysis in experimental design.

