### Collection and clinical information

Sociodemographic data for all participants will be collected from medical records, including information on age, gender, education level, occupation, and other relevant factors. Additionally, clinical data obtained during hospitalization will be recorded, such as vital signs, pupillary response characteristics, need for intubation, surgical interventions performed, imaging results, length of stay in the intensive care unit (ICU), and total hospitalization duration, among other clinical parameters. These data are crucial for a comprehensive characterization of the patients' social and clinical profiles. This detailed information will enable a more thorough analysis of the variables associated with traumatic brain injury (TBI) and will contribute to the development of more precise and individualized management strategies.

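### Table 1's only severity criterion does not separate a low GCS caused by the head injury from one caused by sedation or another complication, so the cohort may be a mixture of unknown composition

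*Protocol article*

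**What the plan says.** Description of protocol, Table 1, requires "Glasgow Coma Scale (GCS) ≤ 8 at any time during hospital stay", ICU admission, age 18 or over and signed consent. It excludes minors, open TBI and previous neurological or psychiatric disease. The GCS line is the only one about severity.

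Patients are found by reading the records of all trauma admissions daily: "This will enable the identification of cases of traumatic brain injury (TBI) and determine the eligibility of patients for inclusion in the study". The aim in the Background is to "evaluate the predictive potential of EEG biomarkers for prognosis, clinical outcomes, and functional recovery in severe TBI patients". The Abstract and the Data collection protocol section also speak of severe TBI.

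The Data collection protocol section places the EEG straight after transfer from the ICU to the ward, in a subacute phase that starts on day seven.

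**The concern.** The time clause in Table 1 is an explicit rule, not a detail lost in condensing an article. Applied as written, one charted score of 8 or less qualifies, whatever produced it and whenever it occurred. Two examples show the gap. One is a patient with a mild closed head injury who is sedated and ventilated around an extracranial operation. The other is a patient with an admission GCS of 14 who falls to 8 because of sepsis. A first low score on the ward would also qualify, although the EEG time point has by then passed.

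At stake is whether the result describes the population named in the aim. Discrimination and correlation both depend on case mix. If membership of the cohort depends partly on sedation practice and in-hospital complications, the estimate cannot be read cleanly as the value of EEG within severe TBI.

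**Working it through.** **1. Does other text close the gap?**

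- *Case finding* (Description of protocol) requires that the patient has a TBI. It does not require that the TBI caused the low score.
- *ICU admission* makes sedation and ventilation more likely, so it does not filter them out.
- *Collection and clinical information* records "need for intubation, surgical interventions performed, imaging results, length of stay in the intensive care unit (ICU"), but none of these items affects eligibility.
- *Table 2* describes the GCS ("Assesses the patient's level of consciousness based on three parameters: eye opening, verbal response, and motor response") without a rule for sedated or intubated patients.
- *Limitations* names treatments, medication and comorbidities as influences on the EEG, not on the qualifying score.

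Nothing shown closes it.

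**2. The plan's own figure.** Inputs from Description of protocol: r = 0.3, two-sided alpha 0.05, power 0.80. Fisher z gives n = ((1.960 + 0.842)/atanh 0.3)² + 3 = 84.93, rounded up to 85. With the bias-corrected form, power at n = 84 is 0.7996. The stated 84 is reproduced, and this point does not change it.

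**3. Illustration of upward bias.** All inputs are assumed. Scores are normal with SD 1, and higher means more slow activity. Unfavourable outcome is 50% in severe TBI and p in the added patients. The added patients make up a share f, score s lower on average, and have no EEG–outcome relation among themselves. Within severe TBI the score differs by d between outcomes: d = 0 gives AUC 0.50, and d = 0.545 gives AUC 0.65.

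The added patients' share among unfavourable outcomes is a = fp/[0.5(1−f) + fp]. Among favourable outcomes it is b = f(1−p)/[0.5(1−f) + f(1−p)]. Then

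AUC = (1−a)(1−b)Φ(d/√2) + (1−a)b Φ((d+s)/√2) + a(1−b)Φ(−s/√2) + 0.5ab.

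For f = 0.20, p = 0.10, s = 0.5, d = 0: a = 0.02/0.42 = 0.0476 and b = 0.18/0.58 = 0.3103. AUC = 0.3284 + 0.1886 + 0.0119 + 0.0074 = 0.536.

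| f | p | AUC within severe TBI | Apparent AUC, s = 0.5 | Apparent AUC, s = 1.0 |
|---|---|---|---|---|
| 0.05 | 0.10 | 0.50 | 0.511 | 0.520 |
| 0.20 | 0.10 | 0.50 | 0.536 | 0.568 |
| 0.30 | 0.10 | 0.50 | 0.549 | 0.593 |
| 0.20 | 0.10 | 0.65 | 0.674 | 0.697 |
| 0.20 | 0.30 | 0.65 | 0.644 | 0.653 |

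The last row shows that the rise disappears when recovery in the added patients is less good. With f = 0.20, p = 0.10 and no EEG difference (s = 0), 0.65 becomes 0.643. With the same 50% outcome rate and s = 0, it becomes 0.8 × 0.65 + 0.2 × 0.5 = 0.62.

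**4. Illustration of dilution.** Assume that EEG and outcome are uncorrelated in the share f and that the marginal distributions are equal. Then r = 0.3(1−f).

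| f | r | Power at n = 84 | n for 80% power |
|---|---|---|---|
| 0 | 0.30 | 0.80 | 85 |
| 0.10 | 0.27 | 0.71 | 106 |
| 0.20 | 0.24 | 0.60 | 135 |
| 0.30 | 0.21 | 0.49 | 176 |

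Steps 3 and 4 point in opposite directions, and the documents do not say which applies.

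**The case against.** A reader might infer that the cohort is not a severe-TBI cohort, that the AUC will be inflated, or that 84 patients are too few. The documents support none of these. Patients with truly severe TBI also meet the criterion. The direction of bias depends on who else is admitted. The calculations above rest on assumed shares, outcome rates and EEG differences. Even the 20% null shift of 0.036 to 0.068 is only about 0.6 to 1.1 standard errors of an AUC at n = 84 (about 0.06 with 42 patients per outcome).

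There are four further arguments against the point:

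- **Late deterioration can belong to TBI.** The Background says of the inflammatory response: "This inflammation often leads to secondary brain injuries, exacerbating neurological and functional complications". A wide window may be a deliberate way to capture it. This stands: a later fall in GCS is not in itself misclassification, and the documents give no basis for a fixed early window such as 48 hours.
- **The schedule filters some patients.** An EEG from day seven onward, straight after ICU transfer, does not suit a short ICU stay for an operation. This stands in part. It narrows that example, but it is not an eligibility criterion and does not remove long-stay sedated patients.
- **A patient who first qualifies on the ward has already missed the EEG.** Such a patient adds no on-schedule EEG value, so the effect on the AUC is small. What remains is that the criterion and the measurement schedule do not fit together.
- **Scoring rules for sedated patients may sit in a full protocol that is not shown.** That is possible, and their absence here is not the point. The point is the stated time clause, which such a rule would not narrow to a period before the EEG.

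**Conclusion.** The point holds in a limited form. As worded, Table 1 does not distinguish a low score due to the head injury from one due to sedation, anaesthesia or a non-TBI complication, and it can be met after the EEG time point. The cohort may therefore be a mixture of unknown composition, and the EEG–outcome association may be biased upward or diluted. The size cannot be derived from the documents. At an assumed 20% share, the illustrations run from an apparent AUC of 0.54 to 0.57 where the true value is 0.50, to a loss of power from 0.80 to 0.60. The sample-size calculation itself is not in question. The wording should be changed because, without the circumstances of each qualifying score, the mixture may not be recoverable at analysis.

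**What to change.** Reword the GCS line of Table 1 so that the qualifying score of 8 or less

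- is attributed to the closed TBI;
- is scored without the effect of sedation or neuromuscular block, or is the last reliable score before sedation or intubation;
- is reached before ICU discharge, and so before the EEG.

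Keep late deterioration attributed to the TBI eligible, but flag it and repeat the main analysis without the late qualifiers. The sponsor should state what counts as late. A fixed 48-hour window is one option and is not required. Record the date, time and sedation status of the qualifying score from the chart. If the present wording is kept, narrow the conclusion from severe TBI to patients who met the criterion as written.

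The cost is one reworded line, a few fields from charts that are already read daily, one sensitivity analysis and slightly slower accrual.
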